### **Unsolicited Adverse Events**

Space will be provided in the CRF for the recording of unsolicited symptoms. Unsolicited symptoms are any AEs reported by the subjects or their parents within 30 days of a vaccination that are different from those solicited symptoms recorded during the 7 day post-vaccination follow-up period. Should any general (systemic) signs or symptoms be reported, their relationship with the study vaccine will be assessed by the investigator and transcribed into the CRF, as described in Section 11.3.

## Assessment of Intensity

Intensity of solicited AEs will be assessed and graded by the investigator as presented in Table 13.

| **Table 13. Assessment of Solicited Adverse Event (AE) Intensity** | | |
| --- | --- | --- |
| **AE** | **Grade** | **Intensity Definition** |
| Pain at injection site | 0 | Absent |
|  | 1 | Minor reaction to touch |
|  | 2 | Cries/protests on touch |
|  | 3 | Cries when limb is moved/spontaneously painful |
| Swelling at injection site | 0 | Absent |
|  | 1 | < 5 mm |
|  | 2 | 5-20 mm |
|  | 3 | > 20 mm |
| Fever | 0 | < 37.5°C |
|  | 1 | 37.5-38.0°C |
|  | 2 | 38.1-39.0°C |
|  | 3 | > 39.0°C |
| Irritability/Fussiness | 0 | Behavior as usual |
|  | 1 | Crying more than usual/ no effect on normal activity |
|  | 2 | Crying more than usual/ interferes with normal activity |
|  | 3 | Crying that cannot be comforted/ prevents normal activity |
| Drowsiness | 0 | Behavior as usual |
|  | 1 | Drowsiness easily tolerated |
|  | 2 | Drowsiness that interferes with normal activity |
|  | 3 | Drowsiness that prevents normal activity |
| Loss of appetite | 0 | Normal |
|  | 1 | Eating less than usual/ no effect on normal activity |
|  | 2 | Eating less than usual/ interferes with normal activity |
|  | 3 | Not eating at all |

NB: These intensity grades for solicited AEs are consistent with the intensity grades for the same events presented “Table 5: General Toxicity Table”, except that in Table 5 the grade 3 intensities (for all 6 events) are further divided into grade 3 and 4 intensities.

For each solicited symptom, the subject’s parent(s) will be asked if medical advice was sought (i.e. contact attempted with medical personnel) for this symptom.

For all other AEs, maximum intensity should be assigned to one of the following categories:

0 = No adverse event

1 = An adverse event that is easily tolerated by the subject, causing minimal discomfort and not interfering with everyday activities.

2 = An adverse event that is sufficiently discomforting to interfere with normal everyday activities.

3 = An adverse event that prevents normal, everyday activities. (Such an adverse event would, for example, prevent attendance at school, church or other typical assemblies, and would necessitate the administration of corrective therapy.)

## Assessment of Causality

Every effort will be made by the investigator to explain each AE and determine its causal relationship, if any, to administration of the study vaccine.

The degree of certainty with which an AE can be attributed to administration of the study vaccine (or alternative causes, e.g., natural history of underlying diseases, concurrent therapy, etc.) will be determined by how well the event can be understood in terms of one or more of the following:

- Reactions of a similar nature having previously been observed with this type of vaccine or formulation.
- The event having often been reported in literature for similar types of vaccines.
- The event being temporally associated with vaccination or reproduced on re-vaccination.

All solicited local (injection site) reactions will be considered causally related to vaccination.

Assessment of causality in all other AEs should be documented by the investigator by answering the following query on the “Serious and Unexpected Adverse Event Report”:

In your opinion, did the vaccine(s) possibly contribute to the adverse event?

NO; Either the adverse event is not causally related to administration of the study vaccine or

there are other, more likely causes and administration of the study vaccine is not suspected

to have contributed to the adverse event.

YES; There is a reasonable possibility that the vaccine contributed to the adverse event.

Non-serious and serious AEs will be evaluated as two distinct events given their different medical nature. If an event meets the criteria to be determined “serious” (see Section 11.5.1 for definition of an SAE), it will be investigated by the PI to the extent that a determination of ALL relevant contributing factors can be made.

A partial list of possible contributing factors might include:

- Past medical history
- Concurrent medications
- Protocol required procedures
- Lack of efficacy of the test vaccine
- Erroneous vaccine administration

## Adverse Event Follow-up & Assessment of Outcome

Investigators should follow-up subjects with SAEs until the event has subsided, or until the condition has stabilized, regardless of when this occurred in relation to the study conclusion. Investigators should follow-up subjects with non-serious AEs until study conclusion for a given subject. Thus, all follow-ups for a given cohort end on the same calendar day, but the day follow-ups end is different for each cohort. This will be exactly 8 months after the last subject of a given cohort was enrolled into the study. Re-ports relative to the subsequent course of an AE noted for any subject must be submitted to the Study Monitor.

Outcome should be documented as one of the following:

1 = Recovered without sequelae

2 = Recovered with sequelae

3 = Ongoing at subject study conclusion

3a = Ongoing and worsened

3b = Ongoing, but improved

3c = Ongoing and unchanged

4 = Died

5 = Unknown

## Serious Adverse Events

### **Definition of a Serious Adverse Event**

A *serious adverse event* (SAE) is any untoward medical occurrence that results in death, is *life threatening*, results in persistent or significant *disability or incapacity*, requires in-patient *hospitalization* or prolongation of existing hospitalization or is a congenital anomaly or birth defect in the offspring of a study subject. In addition, important medical events that may jeopardize the subject or may require intervention to prevent one of the other outcomes listed above should be considered serious. (Examples of such interventions include intensive treatment in an emergency room or at home for allergic bronchospasm; blood dyscrasias or convulsions that do not result in hospitalization; and development of drug dependency or drug abuse.)

Although not considered to be (or reported as) SAEs, elective hospitalizations and cancers diagnoses should be reported in the same way as SAEs.

Additional definitions of terms used in the above definition of an SAE are:

Life threatening: An adverse event is life threatening if the subject was at risk of death at the time of the event; it does not refer to an event that hypothetically might have caused death if it were more severe.

Disabling or incapacitating: An adverse event is incapacitating or disabling if the event results in a substantial disruption of the subject's ability to carry out normal life functions. This definition is not intended to include experiences of relatively minor medical significance such as headache, nausea, vomiting, diarrhea, influenza, and accidental trauma (e.g. sprained ankle).

Hospitalization: In general, hospitalization signifies that the subject has been detained (usually involving at least an overnight stay) at the hospital or emergency ward for treatment that would not have been appropriate in the physician’s office or other out-patient setting.

Routine Clinical Procedure: A procedure which is defined in the protocol as one which may take place during the study period and should not interfere with the study vaccine administration or any of the ongoing protocol specific procedures.

**If anything untoward is reported during an elective procedure, that occurrence must be reported as an AE, either ‘serious’ or ‘non-serious’, according to the usual criteria.**

**When in doubt as to whether ‘hospitalization’ occurred or was necessary, the event should be considered an SAE.**

### **Reporting Serious Adverse Events**

In the event that any SAE is suspected of being related to vaccination in any study subject, no further vaccinations will be administered to any study subjects until a written report has been submitted to the sponsor (i.e., Office of the Surgeon General, U.S. Army; POC: [name], USAMMDA, [name], USA), GSK Biologicals, MVI, the DSMB, and the FDA, and the investigators have conferred with the LMM.

Any SAEs that are both serious *and* unexpected, whether or not they are judged to be related to the study vaccine or comparator vaccine, will be immediately reported by e-mail or telephone to the USAMRMC Office of Regulatory Compliance and Quality [contact]) (during non-duty hours call [contact] **and** send information by facsimile to [contact]). A written report will follow the initial report within 3 working days. The report will be addressed to the U.S. Army Medical Research and Materiel Command, ATTN: MCMR-RCQ, [name]. In addition, the following agencies will also receive copies of the written report and so will be within 3 working days: the sponsor, WRP/KEMRI Ethics Review Committee, the LMM, the DSMB, GSK Biologicals and MVI. Every SAE that is not resolved at the time the initial written report is filed will have a follow-up report submitted when information is avail-able. Any submitted report will be identified as "initial," "follow-up," or "medical monitor".

An initial notification should include:

• Study protocol number and the name of the PI

• Subject ID number, initials, age and gender

• Date of onset of the event and date of the most recent administration of the study vaccine

The PI will not wait to collect additional information to fully document the event before making notification of an SAE. The telephone or email report should be followed by a full written report utilizing the “Serious Adverse Events Form” within the CRF, detailing relevant aspects of the SAEs in question.

Instances of death, cancer or congenital abnormality in offspring if brought to the attention of the investigator AT ANY TIME after cessation of study test article AND suspected by the investigator to be related to study medication, should be reported to the Study Monitors.

All information should be sent PROMPTLY **by the PI to the sponsor (i.e., Office of the Surgeon General, U.S. Army; POC: [name], USAMMDA, [name], USA), the WRAIR Human Use Research Committee, WRP/KEMRI Ethics Review Committee, MVI, GSK Biologicals, the DSMB and the LMM.** Points of contact for these institutions and committees are given below.

## Treatment of Adverse Events

Treatment of any AE is at the sole discretion of the investigator or the LMM and should be in accord with accepted, local standards of good medical practice. The applied measures should be recorded in the source documents of the vaccinee. The recording of AEs is an important aspect of study documentation. It is the responsibility of the investigator to document all AEs according to the detailed guidelines set out herein. The subjects’ parents will be instructed to contact the PI immediately should a subject manifest any sign or symptom perceived as serious.

# SUBJECT COMPLETION & DROP-OUT

## Definition of a Drop-out

From the perspective of data analysis, a 'drop-out' is any subject who is not brought back for the concluding visit foreseen in the protocol. A subject who is brought in for the concluding visit foreseen in the protocol is considered to have completed the study and is therefore not a drop-out.

## Procedures for Handling Drop-outs

Investigators should make an attempt to contact parents of those subjects who have not been brought for scheduled visits or follow-up. Information gathered should be described on the Study Completion page of the CRF and in source documents (progress notes).

## Reasons for Drop-outs

The Study Completion page of the CRF will specify which of the following possible reasons were responsible for drop-out of the subject from the study:

• Serious adverse event (SAE)

• Non-serious adverse event (AE)

• Protocol violation (Specify)

• Withdrawal of parental consent, not due to an AE or SAE

• Migration of family or subject from the study area

• Loss to follow-up

• Other (Specify)

# DATA MANAGEMENT & ANALYSIS

Data entry will be performed on site at the WRP Kombewa Clinic. Duplicate CRF pages will be removed by the study coordinators periodically (after review and/or approval of the study monitors) and submitted to the data entry center. Data analysis and reporting will be done by Statistics Collaborative, Inc., Washington, DC, USA.

## Primary Endpoints

Occurrence of solicited symptoms during a 7 day follow-up period after each vaccination (5 visits: day of vaccination and days 1, 2, 3, and 7)

Occurrence of unsolicited symptoms during a 30-day follow-up period after vaccination (day of vaccination and 29 subsequent days)

Occurrence of any SAEs during an 8 month follow-up period following the first dose of study vaccine (i.e., 6 months following the last dose)

## Secondary Endpoints

Anti-MSP-1 antibody titers at timepoints at which blood samples are taken for serology.

## Study Cohorts & Data Sets to be Evaluated

### **Total Cohort**

The “total cohort” will include all subjects enrolled in the study.

### **Safety Cohort**

The “safety cohort” will consist of all subjects who have received at least one dose of study vaccine or comparator vaccine and for whom any data on safety are available for analysis. A subset of the safety cohort will include those who received the test article vaccine.

The presentations of safety data will explore separately the adverse experiences among subjects who received all 3 vaccinations and among those who received fewer; among those who received each of the 3 vaccine doses; and among those with clinically important violations of study protocol.

### **Immunogenicity Cohort**

The “immunogenicity cohort” will include all subjects for whom assay results are available for antibodies against the specified study vaccine antigen component or the comparator. There are no standard “cut off” titres for seropositivity determinations in general use for this assay.

## Sample Size

This phase I trial consists of what are essentially 9 small treatment groups (10 subjects each) and 9 small control groups (5 subjects each; See Table 2, Section 7.2). It does not have adequate power to detect small differences between groups. Although comparative statistics for the safety variables will be calculated, the study will have low power to detect anything other than large differences in the incidence of local and general side effects between the vaccination groups. It will be more useful and significant to compare symptom rates for the test article recipients of entire cohorts (N=30) versus that cohort’s comparators (N=15), rather than, for example, Cohort A’s 12-23 month olds receiving FMP-1 (N=10) versus Cohort A’s 12-23 month old Imovax® recipients (N=5).

Sample size was chosen after weighing the need to detect any possible untoward reactions against the need to limit the number of subjects involved for safety purposes. A total sample size of about one hundred (135 in this case) is typical for the initial assessments of the safety, tolerability, and immunogenicity of an investigational vaccine. Incorporation of the Imovax® Rabies vaccine comparison group will enable broad initial estimates of the incidence of local and general side effects and of immune responses among vaccine recipients.

**13.5 Final analyses**

### Analysis of Demographics

Demographic characteristics (age, gender, etc) of each study cohort will be tabulated. The mean age (with range and standard deviation) by gender of the enrolled subjects, by dose group, and in aggregate, will be reported.

### Analysis of Immunogenicity

For each dose group and age group, and at each time point, anti-MSP-1 antibody levels will be presented as geometric means of OD units with 95% confidence interval tabulated. The time course of antibody levels will be described through longitudinal models.

### Analysis of Safety

The overall percentage of subjects with at least one local AE (solicited and unsolicited) and the percentage with at least one general AE (solicited and unsolicited) during the four-day follow-up period after vaccination will be tabulated. The incidence, intensity, and relationship of individual solicited symptoms over a one week period of follow‑up (day of vaccination, plus days 1, 2, 3, and 7) will be calculated per age group and dose.

The number of subjects with at least one report of unsolicited AE, classified by the “World Health Organization Preferred Terms”, reported up to 30 days after vaccination will be tabulated by age group and dose. The intensity and relationship to vaccination of the unsolicited symptoms reported will also be assessed.

SAEs are expected to be rare, but where observed will be described. Comparisons of incidence of all symptoms, local symptoms and general symptoms will utilize a two-sided Fisher’s Exact Test. Analysis of safety during the 8-month follow-up period (6 months after dose 3) will consist of comparison of incidence of SAEs as well as hemoglobin levels.

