**Day 7  3 days Day 7 Post-vaccination 1 follow-up visit**

***Visit 6***

- Record vital signs (temperature, blood pressure, pulse)
- Examine site of injection
- Record solicited and unsolicited AEs (of previous 4 days)
- Complete physical examination
- Check concomitant medications

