| Review of Health Status**k** |  |  |  |  |  |  |  |  |  |  |  |  |  |  | x |
| Scheduled blood volumes | 2 | 2 | 0 | 0 | 2 | 2 | 0 | 0 | 2 | 2 | 0 | 0 | 2 | 2 | 6 |
| **Cumulative** Blood Vol. (mL) | 2 | 4 | 4 |  | 6 | 8 | 8 |  | 10 | 12 | 12 |  | 14 | 16 | 22 |
| 1. Visit numbers & Study day numbers are the same (with slight variations for the latter) for all cohorts; Days/dates for doses 2 & 3 are for planning purposes & are provisional only. 2. Performed within 35 days prior to randomization. 3. Blood collected just before immunization. 4. Limited to Hgb, WBC, lymphocytes, platelets; Hgb determination every 3 mo from Study days 120 to 364. 5. Serum for MSP-1 antibodies collected every 3 mo from Study day 120 to 364 6. Pre-dose, post dose and 60 min after each dose. 7. Solicited symptoms collected for 4-days and on day 7 after each dose. Unsolicited AEs collected for 30 days after each dose. 8. SAEs collected from 1st injection (Study day 0) through 6 months (180 days) after the last injection (Study day 240). 9. Concomitant medications collected through 30 days after last dose of study vaccine. 10. Monthly field worker visits to check on status of subjects. 11. Record any new onset chronic or acute diseases or other medically significant conditions, unscheduled clinic visits, and any new treatments since previous scheduled study visit. | | | | | | | | | | | | | | | |

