### **Recording of Adverse Events**

At each visit/assessment, all AEs either observed by the investigator or one of his clinical collaborators or reported by the subject’s parent(s) spontaneously or in response to a direct question will be evaluated by the investigator. AEs not previously documented in the study will be recorded in the Adverse Event Form within the subject's CRF. The nature of each event, date and time (where appropriate) of onset, outcome, intensity and relationship to vaccination will be established. Details of any corrective treatment should be recorded on the appropriate page of the source document. See Section 11.5 for instructions for reporting and recording of SAEs.

As a consistent method of soliciting AEs, the subject’s parent(s) will be asked a non-leading question such as:

"Has the child behaved or reported feeling different in any way since receiving the vaccine or since the previous visit?"

N.B. The investigator should record only those AEs having occurred within the time frames defined above, see Section 8.2.

AEs already documented in the CRF, i.e. at a previous assessment, and designated as ‘ongoing’ should be reviewed at subsequent visits, as necessary. If these have resolved, the documentation in the CRF should be completed. If an AE changes in frequency or intensity during a study period, a new record of the event will be started.

Solicited AEs will be elicited for the first 4 days and on day 7 post-immunization and unsolicited AEs will be recorded during a 30-day follow-up period (day of vaccination and 29 subsequent days). SAE’s will be recorded through the 6th month after the last vaccination (through Study month 8). Thereafter, SAEs are not recorded/reported, although malaria episodes are documented and blood samples are collected for immunological testing.

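### The overall any-local and any-general AE percentages stop at Day 3, although the solicited primary endpoint runs to Day 7

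*Protocol*

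**What the plan says.** Section 13.1 of the protocol gives the solicited primary endpoint as "Occurrence of solicited symptoms during a 7 day follow-up period after each vaccination", with five visits on Days 0, 1, 2, 3 and 7. The Summary and section 7.1 agree. The unsolicited endpoint is "Occurrence of unsolicited symptoms during a 30-day follow-up period after vaccination".

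Section 13.5.3 sets three windows:
- Overall percentages with at least one local AE and at least one general AE, solicited and unsolicited together: "the percentage with at least one general AE (solicited and unsolicited) during the four-day follow-up period after vaccination will be tabulated".
- Individual symptoms: "The incidence, intensity, and relationship of individual solicited symptoms over a one week period", with Day 7 listed among the days.
- Subjects with at least one unsolicited AE: up to 30 days.

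The test is described later in the same section: "Comparisons of incidence of all symptoms, local symptoms and general symptoms will utilize a two-sided" Fisher's exact test. No window is attached to it.

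On collection, section 11.1.3 says "Solicited AEs will be elicited for the first 4 days and on day 7 post-immunization", and a footnote to Table 9 says "Solicited symptoms collected for 4-days and on day 7 after each dose". At the Day 7 visit (Visit 6 in section 8.2) the instruction is "Record solicited and unsolicited AEs (of previous 4 days"). Visits 12 and 18 carry the same recall. Table 8 allows each of these visits 7 ± 3 days after the dose.

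**The concern.** The protocol declares a 7-day solicited endpoint and collects data to support it, then builds its pooled reactogenicity percentages on the first four days. It gives no reason for the shorter window.

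The individual-symptom tables cannot stand in for the pooled figures. One child may have several symptoms, so symptom rows cannot be added up to the number of children with at least one event. A child whose first general symptom is fever on Day 5 appears in the fever row but is event-free in the any-general percentage.

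The pooled rates matter because section 13.4 names the comparison of a whole cohort's 30 test-vaccine recipients with its 15 comparators as the more useful one. Section 13.6 says that by-group data will guide dosages and sample sizes in later paediatric trials. With groups this small, a few reclassified children are visible.

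**Working it through.** The protocol states no figure for this quantity, so there is none to reproduce. The check compares day sets and then illustrates the possible effect.

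**Step 1: what the four days are.** Section 11.1.3 and the Table 9 footnote list the first 4 days and Day 7 as separate items, and the scheduled visits are on Days 0, 1, 2, 3 and 7. The four-day period is therefore {0, 1, 2, 3}.

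**Step 2: what falls outside it.**
- Endpoint visits {0, 1, 2, 3, 7} minus {0, 1, 2, 3} leaves {7}, one of the five visits.
- Calendar days {0, ..., 7} minus {0, 1, 2, 3} leaves {4, 5, 6, 7}, four of the eight days.

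These counts describe the window. They do not measure the error, because a child with any event on Days 0 to 3 is counted under either window.

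**Step 3: who is misclassified.** Let q be the probability of at least one event on Days 0 to 3, and r the probability of a first event on Days 4 to 7 given none earlier. Then

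7-day percentage = q + (1 − q)r, and expected children missed per 30 = 30(1 − q)r.

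The documents give neither q nor r. The values below are assumptions chosen to show a range.

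| q | r | Four-day % | 7-day % | Missed per 30 | Chance at least 1 of 30 is missed |
|---|---|---|---|---|---|
| 0.30 | 0.05 | 30 | 33.5 | 1.05 | 66% |
| 0.30 | 0.20 | 30 | 44 | 4.2 | 99% |
| 0.50 | 0.10 | 50 | 55 | 1.5 | 79% |
| 0.70 | 0.05 | 70 | 71.5 | 0.45 | 36% |
| 0.70 | 0.20 | 70 | 76 | 1.8 | 84% |

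Example: 0.50 + 0.50 × 0.10 = 0.55, and 30 × 0.50 × 0.10 = 1.5. The last column is 1 − [1 − (1 − q)r]^30. Over these assumptions the rise is 1.5 to 14 percentage points.

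**Step 4: if the Fisher comparison used the four-day counts.** With assumed counts of 12/30 against 2/15, two-sided p = 0.094. With two more test-vaccine recipients whose first event falls on Days 4 to 7, 14/30 against 2/15 gives p = 0.046. If one comparator child also had a late first event, 14/30 against 3/15 gives p = 0.11. The result can move either way.

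**Step 5: the recall at the Day 7 visit.** On Day 7, a recall of the previous 4 days reaches back to the Day 3 visit. On Day 10, the latest allowed, it reaches back only to Day 6 or 7, depending on whether the visit day is counted, so at least Days 4 and 5 are not covered. On Day 4, the earliest allowed, Days 5 to 7 have not yet happened.

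**The case against.** The strongest reply is that the declared primary endpoints are analysed on their own windows elsewhere in 13.5.3: individual solicited symptoms over one week and unsolicited AEs up to 30 days. This stands. The defect is confined to the pooled percentages. A reader might infer that late reactions vanish from the safety analysis; the text does not support that.

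A reader might also infer that the p-values rest on four-day data. The protocol does not say so. The Fisher sentence names no window, and it covers all symptoms, a category that the four-day sentence does not tabulate. The mismatch reaches the test only if the test follows that tabulation.

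The first four days are also a distinct collection period with daily visits, so a summary of them is coherent in itself. That is a reason to keep the summary with a label. It does not explain why the pooled figures stop short of the endpoint.

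On collection, a reader might infer that events on Days 4 to 7 go unrecorded. Other sections largely answer this for unsolicited AEs. Section 11.1.2 requires all AEs within 30 days of each dose to be recorded, section 11.1.3 prompts the parent about changes since the vaccine or the previous visit, and the Day 14 visits record unsolicited AEs since the last dose. What remains is a conflict of wording between a fixed 4-day recall and a visit that may move by three days.

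Two further points stand. If the overall percentage is taken per child across all three doses, a child is missed only when none of the three four-day windows contains an event, so the effect shrinks. And stretching the pooled general-AE figure to 30 days would add background illness in a holoendemic area (section 4.8), so that extension is not recommended.

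The Reporting and Analysis Plan that the DSMB approves could settle exact windows. The protocol, however, has already fixed this one at odds with its own endpoint.

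**Conclusion.** The mismatch is real and rests on the text alone: the pooled local and general percentages cover Days 0 to 3, while the solicited primary endpoint includes Day 7. Nothing in the protocol explains the difference. Children with a first local or general event on Days 4 to 7 are counted as event-free in the only pooled local and general summaries specified.

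The size is unknown. The range of 1.5 to 14 points, or about 0.5 to 4.2 children per 30, depends entirely on the assumed q of 30% to 70% and r of 5% to 20%, and the Fisher counts are likewise invented for illustration. The point calls for correcting a sentence; it does not undermine the safety analysis as a whole. The recall wording at the Day 7 visits is a secondary inconsistency.

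**What to change.** In section 13.5.3:
- Compute the overall any-local and any-general percentages from the day of vaccination through Day 7.
- State that the Fisher comparisons of all, local and general symptoms use this window.
- Keep the Days 0 to 3 percentages as a labelled supporting summary.
- Leave unsolicited AEs in their existing separate 30-day tabulation.

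In section 8.2, at Visits 6, 12 and 18, replace the fixed 4-day recall with one that runs from the Day 3 visit. This matches the prompt in section 11.1.3 and works wherever the visit falls in its 7 ± 3 day window.

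The cost is a few words in the analysis section and one changed prompt on the visit form, with no added visits, blood draws or children. The pooled percentages may rise slightly and take in a little more background illness.
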